### Trial design

The FAMOUS trial is a prospective multicentre mixed methods study. Patients with at least three chronic conditions across nine participating general practices are eligible to be treated as an intervention group by a trained APN. All patients will be treated by APNs for twelve months. Data on the period of intervention are available as data from health insurance companies or the Association of Statutory Health Insurance Physicians (ASHIP) or data collected by the APN. The intervention group will be compared with a control group of patients from German health insurance who are matched according to age, sex, comorbidity and living in a nursing home. The matching will be performed at a ratio of one FAMOUS patient to two control patients.

Qualitative interviews will take place with GPs, APNs and patients to assess factors that are difficult to capture using quantitative data. This evaluation procedure will be carried out by an independent institution (IMBEI). In addition, the intervention will be assessed in more detail in an internal evaluation from the trial sponsor using a longitudinal design.

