### Sample size

The number of cases was calculated on the basis of the number of emergency contacts after twelve months (primary outcome). Based on literature estimates, it was assumed that the expected number of 2.7 emergency contacts per patient per year could be reduced by approximately 15% to 2.295 emergency contacts. The alpha was assumed to be 0.05. Taking into account the cluster effect and a dropout of 30% and a target power of 80%, this results in 817 patients in the intervention group and 1634 patients in the control group.

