### Statistical and further methods

#### Statistical and further methods for primary and secondary outcomes

Statistical analyses of the independent evaluation take place as a comparison between intervention and control groups. Poisson regression will be used for both the primary and secondary endpoints. Adjustments are made for relevant confounders but not for matching variables. APN practices in the intervention group are not considered clusters because a comparable cluster variable is not available for the control group.

Users of the new form of care (patients, participating primary care physicians, and APNs) will be interviewed in qualitative interviews. The interviews will take place at the end of the intervention period to reflect the experiences made. Additionally, primary care physicians will be interviewed at the beginning of the project to map expectations of the new form of care. It can be assumed that a theoretical saturation – i.e., the point at which new interviews no longer provide additional information – will be reached with *n* = 5 GPs and *n* = 5 APNs. Full data collection from all 9 practices participating in the project will nevertheless be targeted. For patients, a number of *n* = 30 participants is expected to reach theoretical saturation.

Cost analysis from the social health insurance perspective will be performed to evaluate potential savings. Costs will be compared between the intervention and the control group. Total cost analysis and cost analysis within subgroups will be carried out to identify areas with the highest costs or cost savings. These subgroups will be identified through the primary and secondary endpoints. Data for the health economic analysis will be obtained from the participating health insurance. Intangible or nonmedical costs will not be analysed since these data are not available in the insurance dataset.

In the internal evaluation, descriptive and analytical statistical methods are used. The patient’s situation at the beginning and at the end of the APN intervention and the nursing process will be described by statistical indicators such as percentual distribution, mean and standard deviation or median and quartile deviation. Depending on the kind of data and on its distribution, parametric or nonparametric statistical analyses will be conducted (e.g., variance analysis, t test, Mann-Whitney U test or Wilcoxon test).

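### The sample size allows for clustering, but the primary Poisson analysis ignores the nine APN practices; if practices differ, the confidence interval is too narrow and type I error exceeds 5%

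*Protocol article*

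**What the plan says.** Under Trial design, the article describes the intervention arm: "Patients with at least three chronic conditions across nine participating general practices are eligible to be treated as an intervention group by a trained APN". Controls come from health insurance data: "The matching will be performed at a ratio of one FAMOUS patient to two control patients".

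Under Sample size, the article plans for "the expected number of 2.7 emergency contacts per patient per year", which "could be reduced by approximately 15% to 2.295 emergency contacts". It adds "The alpha was assumed to be 0.05" and continues: "Taking into account the cluster effect and a dropout of 30% and a target power of 80" per cent, "this results in 817 patients in the intervention group and 1634 patients in the control group". It prints no ICC, cluster size or design effect.

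Under Statistical and further methods for primary and secondary outcomes, the primary endpoint is to be compared by Poisson regression, with adjustment for confounders but not for the matching variables. On clustering the section says: "APN practices in the intervention group are not considered clusters because a comparable cluster variable is not available for the control group".

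The Additional analyses section announces sensitivity analyses without saying what they are.

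**The concern.** The plan treats practice clustering as large enough to enlarge the trial, then sets it to zero in the primary test. So the stated alpha of 0.05 and power of 80% belong to a different analysis from the one planned.

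Correlation within practices is plausible here. There are nine practices and nine APNs, and each practice's patients share the APN, the GPs and the way patients are approached. APN activities are meant to be chosen flexibly. For patients outside the participating insurer, the APN also records the inpatient data, so outcome capture may differ between APNs too.

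The reason given does not hold. A cluster variable is not needed in both arms, because a model can carry a practice effect in the arm where practices exist and treat each control as independent. At stake are the standard error, confidence interval and p-value of the primary comparison.

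**Working it through.** **Inputs from the protocol article.** Control rate 2.7 and intervention rate 2.295 per patient-year; alpha 0.05 (taken as two-sided, since the article does not say); power 80%; dropout 30%; allocation 1:2; 817 and 1634 patients; nine practices. After dropout: 817 × 0.7 = 572 intervention and 1634 × 0.7 = 1144 control patients, so 572/9 ≈ 64 evaluable per practice (817/9 ≈ 91 enrolled).

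**Step 1: try to reproduce 817.** (1.96 + 0.8416)² = 7.849.
- Rate difference, 1:2: 7.849 × (2.295 + 2.7/2) / 0.405² = 174 evaluable intervention patients, or 174.4/0.7 = 249 enrolled.
- Log rate ratio, 1:2: 7.849 × (1/2.295 + 1/(2 × 2.7)) / (ln 0.85)² = 185, or 184.5/0.7 = 264 enrolled.
- Rate difference, 1:1: 7.849 × (2.295 + 2.7) / 0.405² = 239 evaluable.

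None of these gives 817, because the cluster allowance is not printed. It can only be back-solved.

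**Step 2: implied design effect, if everything beyond dropout is clustering.** 571.9/174.4 = 3.28; 571.9/184.5 = 3.10; 571.9/239.0 = 2.39. With ICC = (DE − 1)/(m − 1) and m = 63.6, the ICCs are 0.036, 0.034 and 0.022.

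**Step 3: type I error when practice is ignored.** Assume independent controls, the same individual-level variance in both arms and a correctly estimated individual-level variance. Then

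true variance / assumed variance = (DE/572 + 1/1144) / (1/572 + 1/1144) = (DE + 0.5)/1.5,

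and the actual two-sided error is 2 × [1 − Φ(1.96/√ratio)].

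| ICC (assumed) | DE = 1 + 62.6 × ICC | Variance ratio | Actual type I error |
|---|---|---|---|
| 0.001 | 1.06 | 1.04 | 5.5% |
| 0.005 | 1.31 | 1.21 | 7.5% |
| 0.01 | 1.63 | 1.42 | 10% |
| 0.02 | 2.25 | 1.83 | 15% |
| 0.05 | 4.13 | 3.09 | 26% |

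At the back-solved design effects:
- DE 2.39: ratio 1.93, error 16%.
- DE 3.10: ratio 2.40, error 21%.
- DE 3.28: ratio 2.52, error 22%.

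**Step 4: simulation check.** Pure Poisson counts, nine practices, 572 against 1144 patients, no true effect, 4,000 runs per setting. The unclustered Poisson test rejected in 4.9% of runs with no practice variation and in 18% with a between-practice coefficient of variation of 10% (ICC about 0.026). This agrees with the formula.

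**Step 5: why a larger N does not help.** DE = 1 + (m − 1) × ICC grows with the number of patients per practice. At an ICC of 0.01 with all 817 patients evaluable (m = 90.8), DE is 1.90 and the error about 12%, against 10% with 572. The larger sample protects power only.

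**Step 6: power of an analysis that respects the clusters.** With DE 3.28 in the intervention arm only, the variance of the log rate ratio is 3.28/(572 × 2.295) + 1/(1144 × 2.7) = 0.00282, so the standard error is 0.0531. The standardised effect is 0.1625/0.0531 = 3.06. Power from the noncentral t distribution is 76% with 8 df and 79% with 10 df. A normal reference would give 86%, but that is too generous with nine clusters.

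**The case against.** The strongest objection concerns size. A reader might infer that the type I error is far above 5% as a matter of fact. The documents do not support that: they print no ICC, and at 0.001 the excess is half a percentage point. The 16–22% range is a back-calculation that gives all the unexplained inflation to clustering. If part of it was an unstated allowance for overdispersion, the cluster share is smaller. For example, a factor of 2 for overdispersion leaves a design effect of 3.28/2 = 1.64, an ICC of about 0.01 and an error of about 10%. (Fitting a plain Poisson variance to overdispersed counts would be a separate error.) Adjustment for confounders may also reduce the variation between practices. All of this stands, and it is why the result is given as a range.

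The design effect of 3.28 also comes from inflating both arms, whereas Steps 3 and 6 apply it to one. Had 817 been sized for clustering in the intervention arm only, the log-rate formula would imply (571.9 × 0.02641/7.849 − 0.1852) × 2.295 ≈ 4.0. This does not help the plan, but it shows that the power figure is illustrative until the sponsor states its assumption.

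A reader might also infer that clustered standard errors would stop a systematic difference between the chosen practices and the insurer pool from being reported as an APN effect. They would not. Practices were selected for their number of suitable patients and their willingness to take part, and that is confounding in a nonrandomized comparison.

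The unspecified sensitivity analyses might include a clustered one, but they would not repair the stated primary analysis.

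**Conclusion.** The point holds in conditional form. The two sections conflict, and the article does not merely leave the matter open: it fixes an unclustered primary analysis for a reason that does not hold. If practices differ, the primary confidence interval is too narrow and the type I error exceeds 5%. With about 64 evaluable patients per practice and independent controls, the error is about 5.5–10% for ICCs of 0.001–0.01 and reaches 15% at 0.02 and 26% at 0.05. It is about 16–22% if the plan's own inflation beyond dropout is all clustering. The direction is certain given any practice variation. The size is only moderately certain, because the ICC is an assumption. Since this affects the primary test and is cheap to correct, it should be corrected before the analysis.

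**What to change.** Replace the sentence on clusters with a partially nested primary analysis. Either of these would do:
- a count model with a random practice effect in the intervention arm only; or
- a practice-clustered variance with each control as its own cluster.

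Both need a small-sample reference distribution suited to nine clusters rather than a normal one.

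In the sample size section, state the ICC or design effect behind 817 and whether it was applied to one arm or both. Then restate the power for the analysis that will be run. As a guide, it is about 76–79% if a design effect of 3.28 applies in the intervention arm only, with 8–10 df.

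**Cost:** wording and a recalculation. Practice is known for every intervention patient, so no data are added. The interval will be wider and the stated power possibly slightly lower. The change corrects the standard error only; selection of practices remains a source of confounding to be dealt with separately.

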### Eligibility criteria

Patients (or a legal representative) must provide written informed consent before any study procedures occur. The inclusion criteria are as follows: at least 18 years of age; medical diagnosis of at least three chronic diseases that have led to GP treatment in at least three out of four quarters in the last twelve months; and insured by statutory health insurance. The exclusion criterion is a life expectancy less than 12 months as assessed by the treating physician.

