### Participant timeline

The initial data of the participating patients includes age, sex, medical diagnoses, and number and duration of illnesses. These data are collected during the enrolment phase. Each patient enrolled in the project takes part in APN care for twelve months. The initial assessment lasts on average 1.5 hours. Follow-up contacts for the implementation and continuation of the care plan usually take place every four weeks. Depending on the need, however, the intervals can also be significantly shorter or significantly longer. APN contact is held at least quarterly. Routine contacts last on average 30 minutes. Depending on patient concerns and needs, the time frame may vary.

Routine data are used to count emergency contacts as the primary outcome measure, which means that there is no time stress for the patients. Secondary data are supplied by the ASHIP and by one health insurance company. However, there are patients for whom not all data regarding hospital and emergency contacts are available from routine data. For them, data are collected by the APNs. These data are also used for the analysis of secondary endpoints and health economic analyses. In addition, 30 patients will be interviewed about their experiences after completion of the 12-month intervention. We do not foresee the need for follow-up data collection.

The assessment tools mentioned above are used to measure the health status of the patients in the internal assessment. Data will be collected at the beginning (t0) and at the end (t1) of the 12-month intervention. Patient satisfaction with APN care is measured using a project-specific questionnaire.

The participants’ timeline in relation to the individual steps that occur during enrolment, intervention and evaluation is shown in Table 2:

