## Methods: data collection, management, analysis

### Data collection methods

For the independent evaluation, data from ASHIP and the health insurance fund will be used for primary and secondary endpoints. To fill in missing data, such as hospital visits for patients with other health insurance, APNs collect health-related data and document patients' emergency and routine visits to any health-related facility (doctor's office, hospital, emergency room). The health insurer provides a data pool for control group matching. All data are transferred to the IMBEI in pseudonymized form. Patients, GPs, and APNs are informed by mailed invitations about the possibility of interview participation and asked to complete a feedback form. Potential interviewees are called via the feedback form, and appointments are made. The qualitative interviews are conducted by telephone using a previously prepared standardized interview guide. There is a separate guide for each interview group, which is finalized after piloting. Interviews are audio recorded and transcribed verbatim.

As part of the internal evaluation, the health status of each participating patient was measured before (t0) and at the end of the patient-individual intervention phase (t1) using the assessment instruments mentioned in the intervention section above as we use the data from these instruments for care and research purposes. Their psychometric data are as follows: DemTect: interrater reliability *r* = 0.993, sensitivity 85.1%, specificity 97% [14]; MNA: internal consistency α = 0.701, test–retest reliability *r* = 0.697 [23]; NRS: with a cut-off point NRS > 4, the sensitivity of ‘unbearable pain’ is 83%, while the specificity is 96.7%, with a cut-off point NRS > 5, the sensitivity is 94%, while the specificity is 85% [24]; PDI: internal consistency α = 0.86, [17]; HAQ: internal consistency α = 0.78–0.98 [25, 26]. The psychometric results of the German translation are as follows: test–retest reliability 0.94, internal consistency α = 0.92, criterion validity 0.76 [27]; MILVA: internal consistency range between α = 0.61–0.94, sensitivity 72%, specificity 59%; [17]. PAINAD-G: internal consistency α = 0.85, interrater stability *r* = 0.80, retest reliability* r* = 0.90 [21]; DEMMI: internal consistency α = 0.83, interrater reliability ICC 0.94 [28].

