### Analysis population and missing data

The data for the analyses come from different sources. The data of the control group and the data of the insured persons of the participating health insurers are assumed to be complete. Data from the ASHIP are available for all patients. Therefore, it can be assumed that the outpatient care data of all patients are complete. Inpatient data of patients who are not insured by the participating health insurance company will be requested from the APN and entered into a database. Subgroup analyses were performed to assess the data quality of these data. Data can be supplemented by means of imputation procedures.

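### Cost data come from one insurer although patients of any statutory insurer are enrolled, and two sections disagree on whether nurse-recorded contacts also enter the cost analysis

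*Protocol article*

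**What the plan says.** All places are in the protocol article.

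- **Who may enrol.** Under Eligibility criteria a patient must be "insured by statutory health insurance". No particular insurer is required.
- **Who supplies routine data.** Participant timeline: "Secondary data are supplied by the ASHIP and by one health insurance company".
- **Patients outside that insurer are expected.** Analysis population and missing data: "Inpatient data of patients who are not insured by the participating health insurance company will be requested from the APN and entered into a database". The same section says that ASHIP outpatient data exist for all patients.
- **Where controls come from.** Data collection methods: "The health insurer provides a data pool for control group matching". Under Trial design, two controls are matched to each intervention patient on age, sex, comorbidity and nursing home residence. Insurer is not a matching variable.
- **The cost comparison.** Statistical and further methods for primary and secondary outcomes: "Costs will be compared between the intervention and the control group", followed by "Data for the health economic analysis will be obtained from the participating health insurance".
- **A second source.** The Participant timeline says that APNs collect data where routine records of hospital and emergency contacts are incomplete, and continues: "These data are also used for the analysis of secondary endpoints and health economic analyses".

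**The concern.** Lower overall treatment costs are part of the stated objective, and the financial impact is listed among the secondary endpoints. The cost comparison therefore needs one defined source and one defined population. The article fixes both in a way that cannot be carried out for the whole intervention arm.

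If the statistical methods section governs, intervention patients of other insurers have no record in the cost source, while all controls do. Controls selected to resemble the whole intervention arm could then be compared with only part of it.

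If the timeline governs, the gap is filled with contacts documented by the APNs. These are counts of visits and admissions, and the article describes no step that turns them into costs. The control arm would be measured by billing records and part of the intervention arm by nurse documentation, so any difference in completeness or valuation between the two would appear as a cost difference.

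**Working it through.** **1. The stated numbers.** 817 × 2 = 1634 and 817 + 1634 = 2451, so the planned sizes agree with 1:2 matching. How 817 was derived depends on a cluster effect whose value is not given. This point does not rely on it.

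**2. The two rules side by side.**

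| | Statistical methods section | Participant timeline (natural reading) |
|---|---|---|
| Source of cost data | participating insurer | routine data plus APN-recorded contacts |
| Intervention patients covered | that insurer's members only | all, but measured in two ways |
| Controls covered | all | all, by billing records |
| Risk | balance on matching variables | measurement differs by arm |

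The two risks are alternatives. They do not add up.

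**3. Size of the covered subset.** Let s be the participating insurer's share of the intervention arm. The article does not give it; 30–70% is an assumption. Counts are before the planned 30% dropout.

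| s | Intervention patients with cost records, 817·s | All controls per such patient, 1634/(817·s) | Own matched controls, 2·817·s |
|---|---|---|---|
| 0.3 | 245 | 6.7 | 490 |
| 0.5 | 408 | 4.0 | 817 |
| 0.7 | 572 | 2.9 | 1144 |

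A ratio other than 1:2 is not in itself a bias.

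**4. When balance is disturbed.** Take a matching variable on which that insurer's intervention patients differ from the other intervention patients by d standard deviations. The arm mean is s·(insurer mean) + (1 − s)·(other mean). If the 1634 controls reproduce the arm mean, the subset differs from them by (1 − s)·d. With an illustrative d = 0.2:

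- s = 0.3: 0.7 × 0.2 = 0.14 SD
- s = 0.5: 0.5 × 0.2 = 0.10 SD
- s = 0.7: 0.3 × 0.2 = 0.06 SD

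The imbalance is zero if d = 0. It is also zero, whatever d is, if each covered patient is compared only with his or her own two controls.

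**5. Price of keeping only intact matched sets.** Assume equal variance per patient, independent observations and equal dropout. The standard error is then proportional to sqrt(1/n + 1/(2n)) = sqrt(1.5/n). With n = 817·s, its ratio to the full comparison is 1/sqrt(s): 1.83 at s = 0.3, 1.41 at 0.5 and 1.20 at 0.7.

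For comparison, the covered subset against all 1634 controls gives sqrt[(1/(817·s) + 1/1634) / (1.5/817)]: 1.60, 1.29 and 1.13. Most of the loss thus comes from the missing intervention records. Dropping the surplus controls adds 1.83/1.60 = 1.14, 1.41/1.29 = 1.10 and 1.20/1.13 = 1.05 (from unrounded values), a further 5–14%.

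**The case against.** The strongest reply is that nothing in the article says the insurer's patients will be compared with all 1634 controls. Matching is per patient, so an analyst who keeps each covered patient's own two controls preserves it, and the choice of analysis set could be made in a document not shown here. This is correct as far as it goes. The conflict between the two sections remains, however, and the only comparison that the article names is between the whole groups.

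Three stronger inferences are tempting, and the documents do not support them.

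- **That the matching is broken.** It is at risk only if the surplus controls are kept and the insurer's patients differ from the others on the matching variables. The article states neither.
- **That a cost difference would reflect membership of a particular insurer.** The controls come from the insurer's pool, so in the insurer-only comparison both sides are its members. Only a difference in age, sex, comorbidity or nursing home residence could enter through the retained controls.
- **That the plan refuses to adjust costs for the matching variables.** That rule is stated with the Poisson regression. No model is given for costs.

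The wording of the timeline is also not beyond doubt: its reference to these data could mean the routine data named just before. The conflict would then disappear, but the incomplete coverage of the intervention arm would apply in full. Finally, other places speak of insurers or funds in the plural. The point stands regardless, because intervention patients outside the participating insurer are expressly foreseen.

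**Conclusion.** The concern holds in a limited form. On the natural reading, the article gives two conflicting sources for the cost data. It also names a whole-group cost comparison that the source in the statistical methods section can supply for only part of the intervention arm. Under that source, imbalance on the matching variables is possible but not shown. Under the timeline, costs would be measured differently in the two arms.

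Neither a direction nor an amount of bias in the cost result can be derived from the documents. They give neither the insurer's share nor any comparison of its patients with the others. The counts of 245–572 rest on an assumed share of 30–70%, and the imbalance of 0.06–0.14 SD rests further on an assumed difference of 0.2 SD. The primary endpoint is outside this point. The matter is worth settling before the analysis because costs belong to the stated objective and the correction is small.

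**What to change.** 1. Reconcile the Participant timeline with the statistical methods section, so that one source is named for the cost data.
2. Base the main cost comparison on insurer billing data in both arms, restricted to matched sets whose intervention patient is insured with the participating insurer. Controls matched to patients of other insurers leave this analysis.
3. Report the resulting numbers of intervention patients and controls.
4. Use APN-recorded contacts for costs only in a sensitivity analysis.

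This takes a few sentences in the analysis plan and a filter on the matched-set identifier; no new data are needed. The downside is fewer patients and a wider interval: a standard error about 1/sqrt(share) times the full one, or 1.2–1.8 for an assumed share of 70–30%. The main cost result would then describe the participating insurer's patients and not the whole intervention arm, and the report should say so.

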	Key inclusion and exclusion criteria	Gender: all genders Minimum age: ≥ 18 years Maximum age: no maximum age Further inclusion criteria: medical diagnosis of at least three chronic diseases, which in the past 12 months in at least three out of four quarters have given rise to general practitioners’ treatment;being in general practitioners’ treatment; insurance with a statutory health insurance company. Exclusion criteria: not fulfilling the inclusion criteria; being in the dying phase according to the assessment of the general practitioner.
	Study type	Interventional, nonrandomized, nonblinded controlled trial
	Date of first enrolment	2021/10/01
	Target sample size	*n*=2451
	Recruitment status	Recruiting
	Primary outcome(s)	Number of emergency contacts
	Key secondary outcomes	Use of other health care facilities (e.g. hospital, nursing home), hospital readmission and visits by general practitioners
3 Protocol version	Issue Date: 2021/10/01	
4 Funding	There was financial support only, provided by the German Innovation Fund of the Federal Joint Committee. The Innovation Fund uses funds from the statutory health insurance (SHI) to support innovative, cross-sectoral new forms of care and patient-oriented care research projects in order to further develop and improve SHI-financed care in Germany	
5a Author details	RS and EG initiated the study design; CDS is responsible for the project management; JK developed the concept of the internal evaluation and will conduct it. EG and MB developed the concept of the external evaluation; BB and MB together with a statistician are planning and will conduct the statistical analysis. BB is responsible for the implementation of the qualitative interviews. All authors contributed to the development and refinement of the study protocol and approved the final manuscript.	
5b Name and contact information for the trial sponsor	Trial Sponsor: Catholic University of Applied Sciences Mainz (CUAS) Contact name: [name]. [name] Address: [name], Germany Telephone: [name] Email: [contact]	
5c Role of funder	This funding source had no role in the design of this study and will not have any role during its execution, analyses, interpretation of the data, or decision to submit results.	

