
In Germany, outpatient medical care is predominantly provided by general practitioners. Unlike in many other countries, APNs are not deployed in general practices in Germany. One reason for this is that for a long time, there were no APN education opportunities at the master’s level in Germany. However, academically qualified nurses are now available thanks to the degree programs that have been established in Germany for some time. The objective of this study is to evaluate the care for multimorbid patients by APNs deployed in general practices in rural areas in Germany.

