#### Secondary endpoints

The secondary endpoints in question are the use of continuing care institutions (inpatient hospitalizations, specialist visits, and nursing home stays), hospital readmission and home visits by primary care physicians. In addition, the expectations and experiences of participating physicians, APNs, and patients are mapped, and the financial impact of the intervention will be measured. The primary and secondary endpoints will be assessed by the IMBEI.

Outcomes of the internal evaluation are the health status of the patients and the satisfaction of physicians, patients and relatives with the APN care. In addition, the role development of the APNs and the experiences of the medical assistants are evaluated.

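### The cost comparison takes its data from the insurer and nowhere adds the cost of the APN service; if that service is grant-paid and absent from those data, net savings would be overstated

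*Protocol article*

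**What the plan says.** The section Statistical and further methods for primary and secondary outcomes sets the perspective and aim: "Cost analysis from the social health insurance perspective will be performed to evaluate potential savings". It then says "Costs will be compared between the intervention and the control group", both in total and within subgroups. It names one source: "Data for the health economic analysis will be obtained from the participating health insurance". The only costs it expressly leaves out are these: "Intangible or nonmedical costs will not be analysed since these data are not available in the insurance dataset". Under Secondary endpoints the article says that "the financial impact of the intervention will be measured".

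Two other places describe the service being evaluated. Background and rationale says "Unlike in many other countries, APNs are not deployed in general practices in Germany". Table 1, item 4, says "There was financial support only, provided by the German Innovation Fund of the Federal Joint Committee", and adds that this fund is itself financed from SHI money.

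The Participant timeline section describes hospital and emergency contacts that APNs record for patients whose routine data are incomplete, and says of them: "These data are also used for the analysis of secondary endpoints and health economic analyses".

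**The concern.** A comparison of insurer costs between groups shows the net effect on the payer only if the cost of the intervention is in the data. Here the intervention is a new service by nine master's-level nurses with 500 hours of project training each, mentoring and weekly case conferences. The article describes no billing route by which this would reach insurer records, and no step that adds it from elsewhere. It also drops other cost types because the insurance dataset lacks them, so presence in that dataset appears to decide what is costed.

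If the APN service is missing, it is missing in one group only, and always in favour of the intervention. The Objectives section expects lower overall treatment costs, so a reported saving could be taken as a net saving to SHI when it is a saving in downstream care alone.

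The data source is a second problem. APN-recorded contacts are described as visits, not as billed amounts. If they enter the cost analysis, patients of other insurers join the intervention group without billed inpatient costs, while all controls come from the insurer's data pool.

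**Working it through.** The article gives no cost figure, so there is none to reproduce. The check has two parts: what the text covers, and how large the uncovered item could be.

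**What the text covers**

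- Source of cost data: the participating insurer (statistical methods section), against insurer data plus APN-recorded contacts (Participant timeline). These differ.
- APN salary, training and mentoring: described under Intervention description and Adherence, but not mentioned in any passage on costs.
- Who pays the APNs: not stated. Table 1 gives the project's funder only.
- Perspective: SHI. Because Table 1 traces the grant to SHI money, the perspective does not by itself justify leaving the service out.

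**APN input from the article's own schedule** (Participant timeline: 1.5 h initial assessment; 0.5 h routine contacts, usually four-weekly and at least quarterly)

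- Usual schedule: 52/4 = 13 contacts; 1.5 + 13 × 0.5 = 8.0 h per patient-year.
- Quarterly minimum: 1.5 + 4 × 0.5 = 3.5 h per patient-year.
- Over 817 patients: 8.0 × 817 = 6,536 h, or 3.5 × 817 = about 2,860 h.

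**Cost per patient under assumed unit costs** (employer cost of EUR 70,000–90,000 per APN-year and 1,600 working hours per year; neither is in the article)

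- Contact time only, usual schedule: 8.0/1,600 × 70,000 = EUR 350; × 90,000 = EUR 450. At the quarterly minimum, 3.5/1,600 × 70,000 = about EUR 153.
- Nine APNs charged for 12 months, full time: 9 × 70,000/817 = EUR 771; 9 × 90,000/817 = EUR 991.
- Nine APNs charged for the 24-month project, full time: 18/817 = 0.022 APN-years per patient; 18 × 70,000/817 = EUR 1,542; 18 × 90,000/817 = EUR 1,983.

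Contact time excludes travel, documentation, case conferences, training and mentoring. Full-time employment is an assumption.

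**Set against the planned effect** (Sample size section)

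- 2.7 − 2.295 = 0.405 fewer emergency contacts per patient-year.
- At an assumed EUR 500–2,000 per contact: 0.405 × 500 = about EUR 203; 0.405 × 2,000 = EUR 810.
- Break-even value per avoided contact: 350/0.405 = about EUR 864; 1,983/0.405 = about EUR 4,896.

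The two ranges overlap: EUR 350, 450 and 771 are all below EUR 810. The saving side also counts emergency contacts alone, whereas the article also hopes for fewer GP visits and measures hospital, specialist and nursing home use. The figures show that the item is not negligible. They do not show which side is larger.

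**The case against.** The strongest reply is that the central premise is an inference. The article nowhere says that the grant pays the APNs or that their service is absent from insurer records, and it places the medical side of care under the delegation model without describing reimbursement. It is also a condensed article: programme costing could sit in a full protocol or a health-economic plan, APN cost is not among the costs expressly excluded, and a comparison of care costs is legitimate if labelled as such. All of this stands, and it is why the point is conditional.

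A reader might infer several stronger things that the article does not support:

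- That only insurer data are used. The Participant timeline section says otherwise.
- That savings are certainly overstated. This depends on the unstated payment route.
- That the net result would reverse. Every euro value is assumed, and the ranges overlap.
- That the car for home visits is an omitted payer cost. Intervention description makes it something the practice provides, so it is not evidently an SHI cost.

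The reply does not remove the point. The source sentence is unqualified, so this is something the article fixes and not merely something it leaves out. Followed as written, it would probably give downstream costs only, under an endpoint worded as the financial impact of the intervention. The possibility of valuing APN-recorded contacts with unit costs, or of imputing, does not settle the conflict between the two sections either, because the article links neither step to costs.

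**Conclusion.** The point holds in conditional form. The article names the insurer as the source for the cost comparison and makes no provision for the cost of the APN service. If that service is grant-paid and not in the insurer's data, the comparison omits it in the intervention group only and net savings would be overstated. The SHI perspective does not excuse this, since the fund is SHI money.

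The amount cannot be computed from the article. On the assumptions shown it is roughly EUR 350 per patient for contact time on the usual schedule, up to about EUR 1,980 if 18 full-time APN-years are spread over 817 patients. A change of sign is possible but not demonstrated.

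The conflict over the data source does not depend on any assumption: the Participant timeline and the statistical methods section describe different inputs to the same analysis and must be reconciled.

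**What to change.** In the statistical methods section, define total cost in the intervention group as insurer cost plus SHI-relevant APN programme cost per patient: APN time valued from the activities that the Auditing section says are already documented, plus training and mentoring. Use a stated range of unit costs, and do not count again anything already billed to the insurer. State who pays for the service, so that a reader can see what the insurer data contain.

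If programme cost is not added, label the result as downstream cost excluding the intervention and make no claim of net savings.

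Reconcile the Participant timeline with the statistical methods section. Base the main cost comparison on intervention patients of the participating insurer and their matched controls, so that both groups have billed costs from the same source. Any analysis that brings in patients of other insurers should be a sensitivity analysis with the valuation of their contacts specified.

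This needs some extra analysis and unit-cost inputs, but no new patient data. The price is a probably less favourable cost result and a smaller sample for the cost comparison.
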